#### Translational ‘SQA’ substudy

SQA is an important component of this trial because LINX is a newer surgical procedure and because there is (inter)national variation in fundoplication techniques. This is the first trial of its kind to embed an SQA programme based on video analysis. The SQA will help to ensure the procedures are also completed to a good surgical standard, to maximize internal and external validity and facilitate accurate interpretation of trial results and replication of the successful intervention across wider clinical practice. Every operation performed within the trial will be video recorded and reviewed as part of the SQA programme.

The SQA programme will consist of five phases:

Surgeon training: Surgeons who have not previously undertaken the LINX procedure will attend a hands-on training day with Johnson and Johnson, followed by two proctored cases. A ‘gold standard’ demonstrative video will be circulated to all participating surgeons along with the competency assessment tools for the LINX procedure and fundoplication to ensure consistency.Credentialling of centres and surgeons: All surgeons who have performed <20 LINX procedures will be required to submit two videos each of them performing the LINX procedure and fundoplication, which will be assessed using a competency assessment tool (described below in phase 3).Standardization of surgical techniques: A competency assessment tool for the LINX procedure will be developed after a virtual Delphi consensus process and robust testing for inter- and intra-assessor reliability for video assessment. The Society of American Gastrointestinal and Endoscopic Surgeons (SAGES) has developed and validated a competency assessment tool for fundoplication, which will be used in the GOLF trial^22^.Mechanistic work: Video assessment will be undertaken for all operations performed within the trial to monitor learning curves and maintain surgical quality.Ongoing monitoring of adherence to the intervention protocols: This will be associated with correlating surgical quality with clinical and patient-reported outcomes.

### Outcomes

#### Primary outcome

Symptomatic reflux and HRQoL assessed using the GORD-HRQoL questionnaire^23^ at 24 months after surgery (*Table 2*).

**Table 2 znaf141-T2:** GERD-HRQoL questionnaire

Please check the number that best reflects your symptoms using the scoring scale provided below	
0 = No symptoms	3 = Symptoms bothersome every day
1 = Symptoms noticeable but not bothersome	4 = Symptoms affect daily activities
2 = Symptoms noticeable and bothersome but not every day	5 = Symptoms are incapacitating—unable to do activities

Check only one box for each question						
How bad is your heartburn?	□ 0	□ 1	□ 2	□ 3	□ 4	□ 5
Heartburn when lying down?	□ 0	□ 1	□ 2	□ 3	□ 4	□ 5
Heartburn when standing up?	□ 0	□ 1	□ 2	□ 3	□ 4	□ 5
Heartburn after meals?	□ 0	□ 1	□ 2	□ 3	□ 4	□ 5
Does heartburn change your diet?	□ 0	□ 1	□ 2	□ 3	□ 4	□ 5
Does heartburn wake you from sleep?	□ 0	□ 1	□ 2	□ 3	□ 4	□ 5
Do you have difficulty swallowing?	□ 0	□ 1	□ 2	□ 3	□ 4	□ 5
Do you have bloating or gassy feelings?	□ 0	□ 1	□ 2	□ 3	□ 4	□ 5
Do you have pain with swallowing?	□ 0	□ 1	□ 2	□ 3	□ 4	□ 5
If you take medication, does this affect your daily life?	□ 0	□ 1	□ 2	□ 3	□ 4	□ 5
How satisfied are you with your present condition?	□ Satisfied		□ Neutral		□ Dissatisfied	

GORD, gastro-oesophageal reflux disease; HRQoL, health-related quality of life.

#### Secondary outcomes

Prevalence of gas bloating measured using participant-reported outcomes/GORD-HRQoL and foregut symptom questionnaire^24^ at 24 months after surgery.Prevalence of inability to belch measured using participant-reported outcomes/GORD-HRQoL and foregut symptom questionnaire at 24 months after surgery.Prevalence of reflux symptoms, inability to belch, and gas bloating measured using participant-reported outcomes/GORD-HRQoL and foregut symptom questionnaire at 6 weeks and 6 and 12 months after surgery.Prevalence and severity of dysphagia and regurgitation measured using participant-reported outcomes/GORD-HRQoL questionnaire at 6 weeks and 6, 12, and 24 months after surgery.Global HRQoL measured using participant-reported outcomes/EQ-5D-5L^25^ questionnaire at 6 weeks and 6, 12, and 24 months after surgery.Utilization of antireflux medications measured using participant-reported outcomes/questionnaire at 6 weeks and 6, 12, and 24 months after surgery.24-h pH measurement or BRAVO test at 12 months after surgery.30- and 90-day and 12- and 24-month postoperative complication rates, including reoperation and endoscopic re-intervention, measured using participant’s medical records/postoperative outcomes.Cost-effectiveness measured using incremental cost per quality-adjusted life year (QALY)^26^ at 6 weeks and 6, 12 and 24 months after surgery.

The total duration of trial recruitment is expected to be 30 months. Patients will be followed up for 24 months after surgery. The GOLF trial will be embedded within the Association of Upper Gastrointestinal Surgeons for Great Britain and Ireland (AUGIS) benign surgical registry, which will permit follow-up reports at 5 and 10 years after surgery. Patient consent will also be obtained to link their data and ensure comprehensive follow-up to assess the long-term outcome and safety of the LINX procedure compared with fundoplication.

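### Regurgitation is assigned only to the GORD-HRQoL, but the form printed in Table 2 has no regurgitation item

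*Protocol article*

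**What the plan says.** The protocol article makes two statements that have to agree.

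- **The outcome.** Under Secondary outcomes: "Prevalence and severity of dysphagia and regurgitation measured using participant-reported outcomes/GORD-HRQoL questionnaire", at 6 weeks and at 6, 12 and 24 months. The GORD-HRQoL is the only questionnaire named in that entry.
- **The instrument.** Under Primary outcome: "Symptomatic reflux and HRQoL assessed using the GORD-HRQoL questionnaire" at 24 months, with a pointer to Table 2, which sets out the form with its scoring key, ten items scored 0 to 5, and a closing satisfaction question.

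Other entries in the same list name a second instrument. For the 24-month belching outcome the text reads "Prevalence of inability to belch measured using participant-reported outcomes/GORD-HRQoL and foregut symptom questionnaire at 24 months after surgery". The entry for the earlier visits begins "Prevalence of reflux symptoms, inability to belch, and gas bloating measured using participant-reported outcomes/GORD-HRQoL and foregut symptom questionnaire at 6 weeks" and goes on to 6 and 12 months.

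**The concern.** An outcome can be scored only if its named instrument asks about it. The article gives both the instrument for regurgitation and every question on that instrument, and the two do not match. This is a conflict between two stated facts rather than a detail left for later. A statistical analysis plan can set a cut-off or a scoring rule, but it cannot derive regurgitation from a form that does not ask about it.

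Regurgitation is a listed efficacy outcome of an antireflux trial. If the form in Table 2 is the one administered, and no other form asks the question, the answers are never collected and cannot be recovered after the visit has passed. The mismatch also raises the question of which version of the primary instrument is in use.

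**Working it through.** The plan gives no figure to reproduce here. The check sets the Table 2 items against the outcomes that the Secondary outcomes list assigns to the GORD-HRQoL.

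**Items in Table 2**

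| Content | Number of items |
|---|---|
| Heartburn (severity, lying, standing, after meals, diet, sleep) | 6 |
| Swallowing (difficulty, pain) | 2 |
| Bloating or gas | 1 |
| Effect of medication on daily life | 1 |
| Satisfaction (three categories, not scored 0 to 5) | 1 |

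Total: 6 + 2 + 1 + 1 = 10 scored items, plus 1 satisfaction question = 11.

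**Match of outcome to item**

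| Outcome | Instruments named | Matching items in Table 2 |
|---|---|---|
| Dysphagia | GORD-HRQoL | "Do you have difficulty swallowing"; also "Do you have pain with swallowing" |
| Regurgitation | GORD-HRQoL | 0 of 11 |
| Gas bloating | GORD-HRQoL and foregut symptom questionnaire | 1 |
| Inability to belch | GORD-HRQoL and foregut symptom questionnaire | 0 of 11 |

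A word search of the 11 items for regurgitation and related terms (food, liquid, acid, vomit) finds nothing. A search for belch or burp finds nothing.

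**Visits.** Regurgitation is due at 6 weeks, 6, 12 and 24 months, which makes four assessments without a matching item. The bloating and belching entries place the foregut symptom questionnaire at 24 months and at 6 weeks, 6 and 12 months, which are the same four visits.

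**Why the version matters for the margin.** Assume that the GORD-HRQoL score is the sum of the ten scored items. Its range is then 0 to 10 × 5 = 50, and the 2-point margin is 2/50 = 4.0% of that range. If a version with k further items scored 0 to 5 were summed instead, the range would be 50 + 5k and the margin 2/(50 + 5k) of it. With k as an assumption, k = 1 gives 2/55 = 3.6% and k = 5 gives 2/75 = 2.7%. The same 2 points would therefore refer to a different scale.

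**The case against.** Four arguments can be made on the other side.

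1. **The data may exist anyway.** The foregut symptom questionnaire is given at all four visits and may ask about regurgitation. Its items are not shown, and the data collection flow chart (Fig. 2) is not available in the text reviewed. This stands. A reader might infer that the trial will collect no regurgitation data, and the documents do not support that. They show only that the one instrument named for the outcome lacks the item.
2. **A condensed article leaves item mapping to the full protocol or analysis plan.** That would excuse silence. Here the article states both sides of the match, and they disagree.
3. **The participant-reported outcomes label could cover another source.** The same label precedes the EQ-5D-5L, so it reads as a data type and not as a second questionnaire. Where the authors intend a second instrument, they name it. Nor can heartburn stand in, because reflux symptoms are listed as an outcome separate from regurgitation.
4. **The belching outcome is covered.** This also stands. Because Table 2 has no belching item, a reader might infer that inability to belch, one of the two core superiority outcomes, cannot be measured. The documents do not show this. The foregut symptom questionnaire is named for it at every time point, and a joint source list need not mean that each form measures each symptom. At most, the GORD-HRQoL is a redundant name there.

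The presence of two instruments for gas bloating is not a fault either. Table 2 has a bloating item, and how the binary outcome is defined is commonly left to the analysis plan.

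**Conclusion.** The point holds for regurgitation alone. As specified, its prevalence and severity cannot be scored at any of the four time points, because 0 of the 11 printed items address it and no other instrument is named. The dysphagia half of the same outcome can be scored.

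The conclusion rests on Table 2 being the complete form. It runs without visible gaps from the scoring key to the satisfaction question. If Table 2 is also the version administered, the error lies in the outcome entry, and the primary outcome, the margin and the core superiority outcomes are untouched. If a longer version is administered, the error lies in Table 2, and the score to which the margin applies needs confirming. The article does not show which of these is the case. The defect is limited in scope and cheap to correct, but it should be settled while the visits can still supply the data.

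**What to change.** 1. Confirm whether Table 2 is the GORD-HRQoL version administered to participants.
2. If it is, check whether the foregut symptom questionnaire has a regurgitation item that supports both prevalence and severity. If so, name it as the source for regurgitation and keep dysphagia on the GORD-HRQoL swallowing items. If not, add one regurgitation question to the electronic form, or remove regurgitation from the outcome list.
3. If a longer version is in use, correct Table 2, name the regurgitation items, and state that the 2-point non-inferiority margin applies to that version's score, or explain which items make up the score.
4. As a minor tidy-up, list the foregut symptom questionnaire alone for inability to belch.

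Cost: a change to the wording of the outcome list or to Table 2, or at most one added electronic question. No change to sample size, visits or the primary analysis is needed if Table 2 is the version in use.

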### Sample size

Sample size calculations were based on a hierarchical analysis and non-inferiority between the study arms for HRQoL including control of reflux (primary outcome) and superiority in favour of the LINX procedure for gas bloating and inability to belch (core secondary outcomes).

#### Non-inferiority outcome

A non-inferiority margin was set at two scores in difference on GORD-HRQoL based on a previous systematic review by the authors^13^, co-investigator consensus, and patient workshops. For a one-sided α level of 0.025 and expecting 10% loss to follow-up, 230 patients per group will be necessary to show non-inferiority with 90% power.

#### Superiority outcomes

A two-sided α level of 0.050 and 10% loss to follow-up were assumed for the superiority outcomes. Regarding postoperative gas bloating, meta-analysis prevalence’s estimate of postoperative gas bloating of 30.1% for fundoplication and a meta-analysis of efficacy showed an OR of 0.34 in favour of LINX^13^, which correspond to a 12.7% prevalence of gas bloating for LINX. Thus, a reduction in postoperative gas bloating of 17.4% (from 30.1% to 12.7%) is hypothesized. According to those parameters, 144 patients per group will be necessary to verify that change with 90% power.

### Randomization

Randomization will be performed using a minimization algorithm to ensure balance between the two treatment groups using stratification factors:

Age (<40, 40–60, and >60 years).Sex at birth (female and male).Co-morbidity at baseline according to the well-validated Charlson Co-morbidity Index (<2 and ≥2).BMI (<30 and ≥30 kg/m^2^).Preoperative DeMeester score (a composite score system of acid exposure during ambulatory pH monitoring used to objectively define GORD) (<14.7 and ≥14.7).Country of treatment (UK and non-UK).24 months after the surgery, patients will be unblinded (that is informed via letter or e-mail about which operation they underwent) and then they will be followed up according to the standard of care in their treating hospital.

### Blinding

This study will be double-blinded (that is the patients and the outcome assessors will be blinded to the trial arms). All postoperative symptomatic questionnaires will be collected electronically directly from blinded patients or by telephone interviews conducted by blinded research nurses and/or blinded central study management staff. At 12 months after surgery, patients will undergo a 24-hour pH study or BRAVO test, as well as manometry investigations, preformed by blinded assessors. Blinding effectiveness will be evaluated for both patients and outcome assessors using the Bang Blinding Index (BBI)^27^. Surgeons and registrars will not be blinded due to the nature of the surgical intervention. The surgeons and registrars will be responsible for adding the patient to the AUGIS benign surgical Registry, which will only be used for follow-up beyond 2 years, when the patients will be unblinded. After randomization, an e-mail confirming treatment allocation will be sent to the principal investigator (unblinded only for participants they randomize) and the delegated operating surgeon. In the event of a serious adverse event, additional site staff may be unblinded if necessary to ensure patient safety.

### Statistical analysis

All analyses will be carried out on the intention-to-treat population (that is all patients will be analysed in the group that they were randomized to regardless of the actual treatment received). It is not anticipated that there will be any protocol deviations; however, in the event that any occur, the primary analysis will be repeated for the per-protocol population (patients excluded from the per-protocol population will be pre-specified in the Statistical Analysis Plan).

Standard descriptive statistics will be used to describe the demographics between the two follow-up regimens; reporting means and standard deviations or medians and interquartile ranges as appropriate for continuous variables and numbers and percentages for binary and categorical variables. All comparative outcomes will be presented as summary statistics and reported together with 95% confidence intervals. All tests will be carried out at a 5% significance level.

The analysis of GORD-HRQoL will be performed using a linear mixed model. This model will produce as output an adjusted GORD-HRQoL score based on the fixed and random effects. It will consider, as the fixed effects, the intervention group, as well as the age, sex, BMI, and preoperative DeMeester score. It will consider, as the random effects, a random intercept by centre. An interaction between the random intercept centre and the intervention will also be included in the model. The model will be run and the output adjusted GORD-HRQoL scores will be compared.

The effect of the LINX procedure on GORD-HRQoL will be tested and quantified through mean differences between groups, adjusted for the factors included in the model; the 97.5% unilateral confidence interval of the mean differences will be provided. A transformation of the primary criterion may be performed to fulfil the assumptions of the linear mixed model.

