## Methods

### Design

The GOLF trial is an international, multicentre, pragmatic, two-arm, double-blind, phase III RCT. The study will recruit 460 patients (230 patients in each of the two arms) recommended for antireflux surgery from at least 16 centres in the UK and 7 other European high-volume upper gastrointestinal surgical centres. Patients will be randomized 1 : 1 to undergo either a laparoscopic/robotic LINX procedure or fundoplication. See *Fig. 1* for the study summary flow chart, *Fig. 2* for the data collection flow chart, and *Fig. 3* for the post-study care and follow-up flow chart.

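### The primary model leaves out Charlson index, a factor the allocation is balanced on, which makes the non-inferiority bound slightly conservative if co-morbidity is prognostic

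*Protocol article*

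**What the plan says.** Under Randomization, the protocol article says: "Randomization will be performed using a minimization algorithm to ensure balance between the two treatment groups using stratification factors". Six factors follow. Four are age, sex at birth, BMI and preoperative DeMeester score. The other two are "Co-morbidity at baseline according to the well-validated Charlson Co-morbidity Index (<2 and ≥2") and "Country of treatment (UK and non-UK").

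Under Statistical analysis, the covariates of the primary model are listed: "It will consider, as the fixed effects, the intervention group, as well as the age, sex, BMI, and preoperative DeMeester score". Two further terms come next: "It will consider, as the random effects, a random intercept by centre", and "An interaction between the random intercept centre and the intervention will also be included in the model". The result is reported as a one-sided bound: "the 97.5% unilateral confidence interval of the mean differences will be provided".

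Under Design, the sites are described as "at least 16 centres in the UK and 7 other European high-volume upper gastrointestinal surgical centres".

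**The concern.** The article names the model type, the covariates, the random terms and the confidence level, so its covariate list reads as complete. That list and the list of minimization factors differ, and the article does not comment on the difference.

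Minimizing on a prognostic factor removes most of that factor's contribution to chance imbalance between arms, so the treatment difference becomes less variable. A model without the factor does not know this. It leaves the factor's variance in the residual and reports a standard error that is larger than the true one. Non-inferiority is decided by one confidence limit against a 2-point margin, so a limit wider than it need be costs some power on the primary question.

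**Working it through.** **1. Compare the two lists.**

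| Minimization factor | Place in the primary model |
|---|---|
| Age | Fixed effect |
| Sex | Fixed effect |
| BMI | Fixed effect |
| DeMeester score | Fixed effect |
| Charlson index (<2, ≥2) | None |
| Country (UK, non-UK) | No fixed effect; centre is nested in country, so it is carried by the random centre intercept |

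Charlson index is the only factor that is wholly absent.

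**2. Put the planned sample size on a usable scale.** The article gives 230 per group, a margin of 2 points, one-sided α 0.025, 90% power and 10% loss. It states no standard deviation, so 230 cannot be reproduced independently, and the SD has to be back-solved.
- Analysed per arm: 230 × 0.9 = 207, or 414 in total.
- n = 2(1.960 + 1.282)² SD² / 2², so SD = √(207 × 4 / (2 × 10.507)) ≈ 6.28.
- Standard error of the difference: 6.28 × √(2/207) ≈ 0.617.
- Distance from estimate to bound: 1.960 × 0.617 ≈ 1.209 points.

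**3. Effect of leaving out a balanced factor.** Let r be the share of outcome variance that the factor explains (an assumption). The model reports a standard error of 0.617, while the true one is 0.617 × √(1 − r). Then:
- one-sided error = Φ(−1.96/√(1 − r))
- power without the factor = Φ((2 − 1.209)/(0.617√(1 − r)))
- power with the factor = Φ(2/(0.617√(1 − r)) − 1.96)

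| Assumed r | One-sided error, factor omitted | Distance to bound, omitted / included | Power, omitted | Power, included | Gain (points) |
|---|---|---|---|---|---|
| 0 | 2.50% | 1.209 / 1.209 | 90.0% | 90.0% | 0 |
| 1% | 2.44% | 1.209 / 1.203 | 90.1% | 90.3% | 0.2 |
| 2% | 2.39% | 1.209 / 1.197 | 90.2% | 90.6% | 0.3 |
| 5% | 2.22% | 1.209 / 1.179 | 90.6% | 91.4% | 0.8 |
| 10% | 1.94% | 1.209 / 1.147 | 91.2% | 92.7% | 1.6 |

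Gains are taken before rounding. The comparison at r = 5% is 90.6% with 91.4%, not 90.0% with 91.4%, because balance alone already gives part of the benefit.

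**4. How large r could plausibly be.** For a two-level factor with prevalence p and a difference of d points between levels, r = p(1 − p)d²/SD². At SD 6.28, r = 5% needs d ≈ 2.8 points at p = 50% and d ≈ 3.9 at p = 15%. r = 10% needs at least 4.0 points. All of these exceed the 2-point margin. At an assumed p = 25%, a 2-point difference gives r = 0.1875 × 4 / 39.4 ≈ 1.9%.

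**5. Simulation of the stated design.** Six-factor minimization, 414 patients, 23 centres (16 UK, 7 non-UK), random centre intercept, 5,000 runs per scenario. Assumed: centre SD 0.8, residual SD 6, Charlson ≥2 in 25%, minimization probability 0.8. The centre-by-intervention term was left out. Monte Carlo error is about 0.2 points on type I error and 0.4 on power.

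| Charlson / country effect (points) | Model | Mean model SE | Type I error | Power |
|---|---|---|---|---|
| 2 / 0 | As stated | 0.598 | 2.7% | 92.4% |
| | Plus Charlson | 0.592 | 2.8% | 92.8% |
| 0 / 2 | As stated | 0.595 | 2.4% | 91.8% |
| | All six | 0.592 | 2.5% | 92.1% |
| 2 / 2 | As stated | 0.601 | 2.6% | 91.6% |
| | All six | 0.592 | 2.6% | 92.1% |
| 4 / 4 | As stated | 0.624 | 2.0% | 90.4% |
| | Plus Charlson | 0.600 | 2.3% | 91.7% |
| | All six | 0.593 | 2.3% | 92.3% |

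Bias was 0.02 points or less throughout. With a 2-point country effect and no Charlson effect, the centre intercept absorbs nearly all of it (0.595 against 0.592). With 4 points each, most of the recoverable loss comes from Charlson (0.624 to 0.600), and country adds a little more (0.600 to 0.593).

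**The case against.** The strongest reply is that the omission errs on the safe side. A bound that is slightly too wide makes non-inferiority harder to claim, not easier, and the estimate stays unbiased. This stands. A reader might infer from the mismatch that the bound is invalid or that the 2.5% error rate is exceeded. The calculation shows the opposite: the error rate is at or below nominal, apart from simulation noise.

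A second reply is that country is already dealt with. This largely stands as well. A reader might count two dropped factors, but a centre belongs to one country stratum, so its intercept takes up most of the country difference. Only a small residue remains, and only when the country effect is large.

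Third, a single binary co-morbidity split would need an effect larger than the non-inferiority margin to explain 5% of variance, and nothing in the article suggests one. This is fair, and it puts the realistic loss at the low end of the range.

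Fourth, a condensed article may leave the reasons for its covariates to the full protocol or the SAP. The absence of a reason is therefore not a fault in itself. What remains is that the article does state a covariate list, and that list leaves out a factor the trial chose to balance on. The article describes no models for gas bloating or belching, so the point cannot be extended to them.

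**Conclusion.** The point holds as a minor inconsistency confined mainly to Charlson index. If that index is prognostic, the primary bound is slightly conservative. One-sided error is about 2.4% at an assumed 1–2% of variance and 2.2% at 5%, with 0.2 to 0.8 points of power given up. If the index is not prognostic, nothing is lost. There is no bias and no added risk of a false non-inferiority claim.

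These figures rest on an SD of about 6.28 back-solved from the sample size, on assumed prognostic strengths, and on a simulation without the centre-by-intervention term. The direction of the effect does not depend on the SD. The case for acting is that the improvement is nearly free, and that fixing the covariates in advance prevents a later choice between two adjusted results should the bound fall close to 2 points.

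**What to change.** Add Charlson index (<2, ≥2) as a fixed effect in the primary linear mixed model. For country (UK, non-UK), either add it as a fixed effect for consistency with the allocation or state that the centre term represents it. Settle the wording before unblinding.

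The cost is a line of text and one or two degrees of freedom out of about 414 analysed patients. Both factors are needed to run the minimization, so no new data are collected and the sample size does not change.

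### The primary model leaves out the baseline GORD-HRQoL score and the 6-week, 6- and 12-month scores, giving up efficiency and protection against informative loss at 24 months

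*Protocol article*

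**What the plan says.** The primary outcome is "Symptomatic reflux and HRQoL assessed using the GORD-HRQoL questionnaire" at 24 months (Protocol article, Primary outcome). The same questionnaire is also given earlier: the Secondary outcomes list reflux symptoms, inability to belch and gas bloating by "GORD-HRQoL and foregut symptom questionnaire at 6 weeks and 6 and 12 months after surgery".

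The Statistical analysis section lists the terms of the primary model. For the fixed part: "It will consider, as the fixed effects, the intervention group, as well as the age, sex, BMI, and preoperative DeMeester score". For the random part: "It will consider, as the random effects, a random intercept by centre", followed by "An interaction between the random intercept centre and the intervention will also be included in the model".

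On the population, the same section says "all patients will be analysed in the group that they were randomized to regardless of the actual treatment received". The Non-inferiority outcome section plans 230 per group "expecting 10% loss to follow-up". The only statements on missing data are in the Health economic analysis section; none concerns the primary clinical outcome. That section names baseline collection for EQ-5D-5L and resource use. The visible text does not say whether GORD-HRQoL is taken at baseline, and the data collection flow chart (Fig. 2) is not shown.

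**The concern.** The model is called a linear mixed model, but the mixing is at centre level only. Without a visit term, a patient effect or a within-patient covariance, it fits one score per patient. Two kinds of information are then left out of the primary estimate: the patient's own score before surgery, and the three post-operative scores before 24 months.

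Two things are at stake. The first is precision: a baseline score that predicts the 24-month score narrows the confidence interval on which non-inferiority is judged. The second is robustness. A patient without a 24-month score adds nothing to such a model unless the score is imputed. If the patients lost are those already doing badly, and this differs between arms, the estimated difference shifts. Non-inferiority is the primary claim, and a shift in favour of LINX would make it easier to declare.

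**Working it through.** **1. Could the model as written use the earlier scores?** Entering all visits into it would treat several scores from one patient as independent, and with no visit term it would not isolate 24 months. The only sensible reading is one 24-month score per patient.

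**2. Loss.** 10% of 460 is 46 patients, 23 per arm. That leaves 414, or 207 per arm.

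**3. The stated sample size.** Inputs from the Non-inferiority outcome section: margin 2, one-sided alpha 0.025, power 90%, 10% loss, 230 per group. The article gives no SD, so 230 cannot be reproduced independently. From n = 2·SD²·(z₀.₉₇₅ + z₀.₉₀)²/margin², with n = 230 × 0.9 = 207 and true difference 0:

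SD = 2 × √(207/2) / (1.960 + 1.282) ≈ 6.28.

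This is a simple two-group calculation that ignores centre-level variance.

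**4. Adding the baseline score.** The residual SD becomes 6.28 × √(1 − ρ²). Here ρ is the correlation of baseline and 24-month scores beyond the covariates already in the model. The documents give no value, so a range is shown. Power is Φ(2/SE − 1.960), with SE = SD × √(2/207).

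| Assumed ρ | Power at 207 per arm | 95% CI half-width | n per group for 90% power, with 10% loss |
|---|---|---|---|
| 0 | 90.0% | 1.21 | 230 |
| 0.2 | 91.1% | 1.19 | 222 |
| 0.3 | 92.5% | 1.15 | 210 |
| 0.4 | 94.3% | 1.11 | 194 |
| 0.5 | 96.3% | 1.05 | 174 |
| 0.6 | 98.2% | 0.97 | 148 |

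**5. Using the earlier scores of lost patients.** Let f be the share of the 23 lost patients per arm who have an earlier score, and r the correlation of that score with the 24-month score (both assumed). The effective n per arm is roughly 207 + 23·f·r².

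- f = 0.5, r = 0.4: 207 + 23 × 0.5 × 0.16 = 208.8; power about 90.3%.
- f = 1, r = 0.8: 207 + 23 × 0.64 = 221.7; power about 91.9%.

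The gain is about 0.3 to 1.9 points of power. With no loss at all (230 per arm) power would be 92.7%.

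**6. Possible bias if nothing is imputed.** Suppose lost patients would have scored D points worse on average than those retained, in both arms, and the loss is a with LINX and b with fundoplication. The retained mean is too low by a·D and b·D, so the LINX minus fundoplication difference is off by D·(b − a). Higher scores are worse, so a negative value favours LINX.

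| Assumed D | Loss 10% / 10% | Loss 12% / 8% | Loss 14% / 6% |
|---|---|---|---|
| 2 | 0 | −0.08 | −0.16 |
| 4 | 0 | −0.16 | −0.32 |
| 6 | 0 | −0.24 | −0.48 |

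Against a margin of 2 this runs from nothing to 24% (0.48/2). If fundoplication loses more patients, the sign reverses. Every D and every split of the loss is an assumption; the documents give only the overall 10%.

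**The case against.** A mixed model of the 24-month score with centre effects is a legitimate analysis of an outcome defined at one time point. It already adjusts for preoperative disease severity through the DeMeester score. The earlier scores are not wasted, since they are analysed as secondary outcomes. All of this stands, and it is why the point concerns a better method and not an invalid one.

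Four stronger readings are tempting, and the documents do not support them.

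- A reader might infer that the primary analysis is a complete-case analysis. The model formula does not settle that: it could be run on imputed data built from the earlier scores. Missing-data handling is commonly left to an analysis plan, which the article says will exist.
- A reader might infer a breach of intention-to-treat. The article's definition concerns the group in which a patient is counted, not what is done when a score is absent. The model and the reference to all patients need to be reconciled, but they are not proven contradictory.
- A reader might infer that a baseline score is being ignored. The visible text does not confirm that GORD-HRQoL is collected at baseline.
- A reader might attach a definite bias to the plan. One simulation with 15% loss concentrated in poor 12-month scorers with LINX, against 5% random loss with fundoplication, gave 0.38 to 0.51 points in favour of LINX. That loss pattern is assumed, and the result depends on how strongly loss is concentrated. The near-zero bias after conditioning on the 12-month score also follows from making loss depend on that observed score alone.

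What the objection does not remove is that the article did not defer the model. It lists the terms, and in the same section leaves only the per-protocol exclusions to the analysis plan. Leaving out the baseline score and any within-patient structure is a stated choice.

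**Conclusion.** The point holds as one of efficiency and robustness. The specified primary model uses neither a baseline GORD-HRQoL score nor the documented scores at 6 weeks, 6 months and 12 months.

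If baseline is collected and correlates 0.3 to 0.5 with the 24-month score beyond the existing covariates, power would be about 92.5% to 96% in place of 90%. Earlier visits would add a smaller 0.3 to 1.9 points. These figures rest on a back-solved SD of about 6.28, a true difference of 0 and assumed correlations.

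The trial has its stated 90% power without the change, so it should not be read as underpowered. The exclusion of about 46 patients, and any bias that follows, are conditional on there being no imputation. The size of that bias depends on the scenario and cannot be taken from the documents.

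**What to change.** - Add the baseline GORD-HRQoL score as a fixed effect, if it is collected; confirm this against the full protocol.
- Estimate the 24-month LINX minus fundoplication contrast from a repeated-measures mixed model of the 6-week, 6-, 12- and 24-month scores. Include treatment-by-visit terms, a within-patient covariance (unstructured, for example) and the centre effect. Multiple imputation of missing 24-month scores from the earlier scores, followed by the single-time-point model, would serve equally well.
- State which patients enter the primary model and how a missing 24-month score is handled, so that this agrees with the reference to all patients.

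The cost is analysis-plan wording, best settled before unblinded data are seen, and slightly more modelling. No new follow-up data are needed, and none at baseline if the score is already taken. Two limits remain. Patients with no post-operative score are still excluded from the repeated-measures version, and both approaches protect only against loss that the observed scores explain.
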